### 4.11 Auditing

This research project will be funded by the Central Council for Research in Ayurvedic Sciences (CCRAS), Ministry of AYUSH. The grant will be utilized strictly as per the approved budget and CCRAS guidelines. All financial records, including bills and receipts, will be maintained in both digital and physical formats and preserved for future audits. Quarterly internal audits will be conducted by the institutional accounts department, and external audits may be carried out by a certified auditor or as directed by CCRAS.

A 6 months progress and financial report will be submitted to CCRAS, including updates on research activities, participant enrollment, preliminary observations, and challenges faced. The financial report will detail fund utilization and be certified by the institutional finance department. Both reports will be submitted in hard and soft copies, and any feedback from CCRAS will be addressed promptly. All procedures will comply with the General Financial Rules (GFR) of the Government of India and institutional norms, ensuring transparency and accountability throughout the study.

## 5 Discussion

Premenstrual syndrome (PMS) represents a significant challenge in women’s health, affecting daily functioning, interpersonal relationships, and overall quality of life. Despite its high prevalence, treatment options often remain limited to symptomatic relief, with pharmacological approaches sometimes associated with side effects or inconsistent acceptability. This underscores the importance of exploring safe, holistic, and patient-centered strategies that not only target symptom reduction but also support long-term wellbeing. Cognitive Behavioral Therapy (CBT) has been consistently reported as an well-established non-pharmacological intervention for mood and anxiety disorders, and emerging evidence highlights its potential relevance in PMS by helping women reframe negative thought patterns, develop adaptive coping skills, and improve emotional regulation. In parallel, *Brahmi* (Bacopa monnieri) holds a respected position in Ayurveda as a *Medhya Rasayana* (nootropic and mind-strengthening herb), traditionally described to enhance memory, concentration, and resilience to stress. Modern pharmacological studies further suggest its role in modulating neurotransmitters such as serotonin and dopamine, reducing oxidative stress, and exerting mild anxiolytic effects, making it worth exploring as a supportive option for PMS-related psychological and somatic symptoms. The novelty of this trial lies in combining these two distinct but complementary approaches. By addressing cognitive patterns through CBT and neurobiological stress responses through *Brahmi*, the study is designed to generate preliminary insights into whether a combined approach may provide broader symptom relief compared to either intervention alone. Importantly, both interventions are non-hormonal, culturally acceptable, and considered safe, which enhances their translational potential in diverse healthcare settings. Methodologically, the trial incorporates several strengths. Participants are screened through standardized tools such as the PSST, PHQ-9, and prospective DRSP diaries, ensuring robust diagnostic confirmation of PMS. The randomized, double-blind design enhances internal validity by minimizing bias, while the use of validated outcome measures including Q-LES-Q-SF and Sheehan Disability Scale ensures that both clinical symptoms and functional impairment are systematically assessed. These choices strengthen the study’s potential to generate initial, reliable observations, even within the constraints of a modest sample size. At a broader level, this work also contributes to the emerging dialogue between traditional systems of medicine and modern psychiatry. While Ayurveda emphasizes balance of body, mind, and environment, CBT provides structured techniques to reframe maladaptive thoughts and behaviors. Integrating the two aligns with the global movement toward holistic, integrative healthcare, where evidence-based traditional interventions are studied with the same rigor as conventional modalities.

## 6 Limitations

This trial is designed as an exploratory study, which in itself places certain boundaries on how the results can be interpreted. By nature, exploratory designs are not meant to provide confirmatory evidence; they mainly help in understanding feasibility and safety. Therefore, the outcomes of this study should be interpreted with caution, as its exploratory character represents the major limitation.

Another limitation comes from the combined intervention model. Since Cognitive Behavioral Therapy (CBT) and *Brahmi* (Bacopa monnieri) will be used together, it will not be possible to know how much each intervention contributes on its own. The results will reflect only the integrated effect of the two, rather than the individual impact of either component.

There are also challenges in aligning the Ayurvedic perspective. PMS and PMDD are not directly identified in classical Ayurvedic texts. Their use in this context is based on correlating symptoms with descriptions found in the literature, rather than on direct reference, which makes the connection more interpretative.

The choice of CBT is supported by earlier studies showing its possible usefulness in PMS and its recognized role in stress- and mood-related conditions. However, it has not yet been included in international guidelines for PMS management. Similarly, while *Brahmi* has a long tradition of use in Ayurveda and growing preclinical support for its role in stress and cognition, it is not a standard treatment in gynecology or psychiatry today.

Taken together, these points underline that this study can only provide preliminary insights into whether a combined CBT–*Brahmi* approach is feasible and potentially helpful. It cannot prove causation or effectiveness. Instead, the findings should be seen as a starting point, paving the way for larger and more definitive studies that can carefully test each component under controlled conditions.

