## Abstract

Premenstrual syndrome (PMS) is a widespread and under-recognized disorder, characterized by cyclical recurrence of physical, psychological, and behavioral symptoms during the luteal phase, significantly impacting the daily functioning of women. Cognitive Behavioral Therapy (CBT) is an established non-pharmacological strategy for PMS, while *Brahmi* (Bacopa monnieri), a classical Ayurvedic herb, has traditionally been used to enhance cognition, reduce anxiety, and support emotional balance. This exploratory study evaluates whether combining *Brahmi* with CBT offers additional benefit compared to CBT alone. It is a double-blind, randomized, placebo-controlled exploratory clinical trial (CTRI/2025/02/081239) conducted at the Amrita School of Ayurveda, Kollam, Kerala, with sponsorship from the Central Council for Research in Ayurveda Sciences (CCRAS). Forty-six women aged 18–24 years, diagnosed with moderate to severe PMS using the Premenstrual Symptoms Screening Tool (PSST) and the Daily Record of Severity of Problems (DRSP), will be recruited and randomly assigned to receive either CBT with *Brahmi* tablets or CBT with placebo tablets. The primary outcomes include reduction in PMS severity, assessed by DRSP, and improvement in quality of life measured with the Quality of Life Enjoyment and Satisfaction Questionnaire (Q-LES-Q SF). Secondary outcome is reduction in functional disability measured using the Sheehan Disability Scale. Assessments will be conducted at baseline, during treatment, and at follow-up. Statistical analysis will be carried out using repeated measures ANOVA with Bonferroni-adjusted post hoc tests, significance set at *p* < 0.05, and effect sizes reported. A limitation of this design is that it cannot disentangle the individual effects of *Brahmi* from CBT, allowing conclusions only on the combined intervention. The study aims to generate preliminary exploratory evidence for a safe, integrative, and accessible approach to PMS management in young women.

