### 1.5 Need for the trial

Premenstrual Syndrome (PMS), if unaddressed, may progress to Premenstrual Dysphoric Disorder (PMDD), affecting mental health and daily life. Early diagnosis and timely care are vital. This trial explores whether combining Cognitive Behavioral Therapy (CBT) with oral *Brahmi* (Bacopa monnieri) tablets offers added benefit over CBT alone in managing moderate to severe PMS.

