## 3 Methods

### 3.1 Trial design

This study is a double-blind, placebo-controlled, randomized exploratory clinical trial designed to generate preliminary observations on feasibility, safety, and potential signals of *Brahmi* (Bacopa monnieri) tablets as an adjunct to Cognitive Behavioral Therapy (CBT) in managing Premenstrual Syndrome (PMS). Eligible participants will be randomly assigned to one of two groups: the trial group (CBT plus Brahmi) or the control group (CBT plus placebo). Randomization will be performed using a fixed block design with a block size of four to ensure balanced group sizes, with the sequence generated by a computer algorithm and maintained by a Medical Officer who is not involved in participant recruitment, intervention delivery, or outcome assessment. Both participants and study personnel involved in delivering CBT, assessing outcomes, and analyzing data will remain blinded to group assignments, ensuring methodological rigor and minimizing potential bias throughout the exploratory trial.

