### 3.4 Interventions

The study intervention will span two menstrual cycles. Participants in the intervention group will receive one-to-one online Cognitive Behavioral Therapy (CBT) sessions, combined with a 500 mg *Brahmi* (Bacopa monnieri) tablet administered once daily after (31, 32) meals with lukewarm water. (33, 34) The control group will receive identical CBT sessions alongside a 500 mg placebo tablet containing inert excipients (dicalcium phosphate, talc, and starch), also taken once daily after food with lukewarm water. Oral medications will be withheld during the menstrual bleeding period for both groups.

The *Brahmi* and placebo tablets were procured from a GMP-certified manufacturer and underwent quality control and analysis to ensure safety, potency, and consistency. Both *Brahmi* and placebo tablets are film-coated to provide uniform appearance, stability, and ease of administration, with the placebo identical in color, shape, and packaging to maintain the double-blind design of the exploratory study.

Cognitive Behavioral Therapy (CBT) sessions will be conducted by two certified CBT therapists, both of whom hold a Master’s degree in Counseling Psychology and formal certification in CBT from accredited institutions. Each therapist has over 2 years of clinical experience in delivering CBT for stress- and mood-related disorders in outpatient settings.

Sessions will be delivered individually (one-on-one) to allow personalized assessment and guidance, ensuring that the intervention is tailored to each participant’s needs. In the event that one therapist is unavailable, the other will continue the intervention without disruption to maintain consistency.

A total of eight sessions will be delivered over two menstrual cycles, on the 5th, 12th, 19th, and 26th days of each cycle, with each session lasting approximately 45 min to 1 h. The CBT protocol is adapted from a previously published study on PMS and includes:

Protocol for Cognitive Behavioral Therapy sessions adapted from a standardized published study on CBT for PMS (7):

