### 4.8 Additional analyses

Subgroup analyses may be undertaken to explore potential differential impacts of therapies based on baseline characteristics such as age, severity of PMS symptoms, menstrual cycle regularity, or baseline psychological distress. Adjusted analyses using multivariate models may also be conducted to account for potential confounders (e.g., BMI, diet, baseline stress levels, or prior PMS-related therapies). These will be explicitly categorized as exploratory and interpreted cautiously. Interaction effects between CBT and *Brahmi* will also be examined if the sample size permits. Exploratory analyses may include treatment adherence, participant satisfaction, and patterns in biopsychosocial variables.

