## 7 Conclusion

This exploratory study provides preliminary observations on the potential of an integrative approach combining Cognitive Behavioral Therapy (CBT) and *Brahmi* in the context of Premenstrual Syndrome (PMS). The design does not permit causal interpretation or allow differentiation of the individual contributions of either intervention, and the findings should therefore be regarded as hypothesis-generating rather than definitive. Within these constraints, the study illustrates the feasibility of examining combined psychological and herbal strategies in women’s health and points to areas where further investigation is warranted. Future research, particularly studies with larger samples, diverse populations, and designs that test each intervention separately as well as in combination, will be essential to clarify their roles and establish a more robust evidence base.

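### Both arms receive CBT, so the trial estimates the add-on effect of Brahmi; the text wrongly says it shows only the combined effect, and the planned CBT-by-Brahmi interaction cannot be estimated at any sample size

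*Protocol article*

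**What the plan says.** All references are to the protocol article.

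**Design.** Section 3.1 randomises participants to "the trial group (CBT plus Brahmi) or the control group (CBT plus placebo"). Section 3.4 adds: "The control group will receive identical CBT sessions alongside a 500 mg placebo tablet". There is no arm without CBT.

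**Question.** Section 1.5 asks whether adding Brahmi "offers added benefit over CBT alone in managing moderate to severe PMS". The hypothesis in 1.6 and the first objective in 2.1.1 put the same add-on question. Section 4.6.7 has the statistician compare outcomes between the two groups.

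**Interpretation.** Other sections describe a different target:
- The Abstract gives as a limitation that the two effects cannot be separated, "allowing conclusions only on the combined intervention".
- Section 3.6 says the design will help to understand the combined effect.
- Section 5 asks "whether a combined approach may provide broader symptom relief compared to either intervention alone".
- Section 6: "The results will reflect only the integrated effect of the two, rather than the individual impact of either component".
- Section 7: "The design does not permit causal interpretation or allow differentiation of the individual contributions of either intervention".

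**Additional analysis.** Section 4.8: "Interaction effects between CBT and *Brahmi* will also be examined if the sample size permits".

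**The concern.** The arms differ only in the tablet, so CBT cancels from the randomised comparison and what remains is the contribution of Brahmi on a background of CBT. The interpretive text turns this round. It presents the combined effect as what the trial delivers, although no arm goes without both treatments to measure it against. It also treats Brahmi's contribution as out of reach, although that is the one thing randomisation isolates.

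The interaction in 4.8 is a related error. It is made conditional on sample size, as if the obstacle were power. The obstacle is that nobody in the trial goes without CBT.

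At stake is what the report may conclude. If the limitation is taken at face value, the valid randomised contrast is disowned and readers are offered a quantity the data cannot supply. An analyst who follows 4.8 will meet a term that the software drops as aliased, or will substitute some other analysis under the same name.

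**Working it through.** **1. The plan's own figure.** Section 4.2.2 sizes the trial for a difference between two group means, with pooled variance 2.85, difference 1.83, and Z values 1.96 and 1.28.

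n = 2 × 2.85 × (1.96 + 1.28)² / 1.83² = 5.70 × 10.4976 / 3.3489 = 17.87, so 18 per group.

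With 20% dropout: 18 / 0.8 = 22.5, so 23 per group and 46 in total.

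This reproduces. The trial is thus sized for the between-arm difference, which is the add-on contrast.

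**2. Model.** Code CBT and Brahmi as 0 or 1 and write

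E[Y] = b0 + b1·CBT + b2·Brahmi + b3·CBT×Brahmi.

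The two arms of sections 3.1 and 3.4 give these rows:

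| Arm | Intercept | CBT | Brahmi | CBT×Brahmi | Mean |
|---|---|---|---|---|---|
| CBT + Brahmi | 1 | 1 | 1 | 1 | b0 + b1 + b2 + b3 |
| CBT + placebo | 1 | 1 | 0 | 0 | b0 + b1 |

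The CBT column equals the intercept column, and the interaction column equals the Brahmi column. There are four parameters and two distinct columns, so the rank is 2.

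**3. What is estimable.** The between-arm difference is (b0 + b1 + b2 + b3) − (b0 + b1) = b2 + b3. A contrast is estimable only if adding its row to the design matrix leaves the rank unchanged. This was checked at 23 and at 1000 per arm, with the same result:

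| Contrast | Parameters | This trial | Four-arm 2×2 |
|---|---|---|---|
| Brahmi added to CBT | b2 + b3 | yes | yes |
| Interaction | b3 | no | yes |
| Combination versus neither | b1 + b2 + b3 | no | yes |
| Combination versus Brahmi alone | b1 + b3 | no | yes |
| Brahmi without CBT | b2 | no | yes |
| CBT alone versus neither | b1 | no | yes |

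A 2×2 factorial has rank 4. It appears here only to show that the missing arms, and not the number of participants, are the cause.

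**4. The text against the table.**
- Sections 1.5, 1.6, 2.1.1 and 4.6.7 match the first row, the only estimable one.
- The combined effect in the Abstract and sections 3.6 and 6 is the third row: not estimable.
- The comparison in section 5 with each component on its own needs the first and the fourth rows. Only the CBT half exists.
- The interaction in 4.8 is the second row: not estimable at any sample size.

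**The case against.** The strongest reply is that the operative parts of the protocol already have the contrast right. The aim, the hypothesis, the first objective, the sample size and the data-management section all concern the two groups compared with each other, and 4.7 allows for changes between groups. The faulty wording sits in interpretive text and in one optional line of a section labelled exploratory. That stands, and it limits the point: no outcome, sample size or planned between-arm estimate is wrong.

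Section 6 is also partly right. Neither the effect of CBT nor that of Brahmi without CBT can be learned, so each component's effect on its own is indeed unknown. The error is the further step to the combined effect being all that is shown.

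One could read the 4.8 interaction as effect modification by CBT sessions attended. The section does not say so, and that would be a non-randomised analysis on a post-randomisation variable, not a CBT-by-Brahmi interaction.

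Two stronger readings are tempting, but the documents do not support them:
- A reader might infer that the report will present the pre-post change in the CBT plus Brahmi arm as the treatment effect. No section plans a single-arm efficacy estimate, and 4.6.7 commits to the between-group comparison. The loose wording leaves this open as a risk and no more.
- A reader might infer that the Abstract, Limitations and Conclusion all deny a causal reading because of the design. The Abstract says nothing about causation, and section 6 puts its caution on causation among limits that it ties mainly to the exploratory nature of the study. Only section 7 attributes the bar to the design.

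The exploratory label is no defence. It limits precision and confirmatory claims. It does not change which contrast the randomisation identifies.

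**Conclusion.** The point holds as an error in the stated target and interpretation, plus one analysis that cannot be carried out. The between-arm difference estimates the effect of Brahmi versus placebo given CBT. The Abstract and sections 3.6 and 6 are wrong to describe the result as the combined effect only. Section 7 is wrong that the design itself bars causal interpretation; a randomised, placebo-controlled comparison permits one for the add-on effect, with limited precision. Section 5 names a comparison for which half the arms are missing. The interaction in 4.8 fails on identifiability (rank 2 for 4 parameters) at any sample size.

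The algebra rests only on CBT being provided identically in both arms, as section 3.4 states. A causal reading of the add-on effect also assumes that randomisation and blinding hold and that missing outcome data do not bias the comparison. No numerical bias is attached, because the planned between-arm estimate is not itself affected.

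**What to change.** 1. In the Abstract and sections 3.6, 6 and 7, state that the trial estimates, with limited precision, the effect of Brahmi versus placebo when added to CBT, by the between-arm difference. State also that it does not estimate the effect of CBT, of Brahmi without CBT, or of the combination versus neither. In section 7, remove the statement that the design does not permit causal interpretation; the cautions on size and exploratory status can stay.
2. In section 5, replace the comparison with each component on its own by a comparison with CBT alone.
3. In section 4.8, delete the CBT-by-Brahmi interaction.
4. In section 4.7, name the between-arm difference as the target of the analysis and label within-arm change as descriptive only.

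Sections 1.5, 1.6 and the first objective in 2.1.1 already state the add-on question and need no change on this point. The cost is wording only: no new arm, no new data, and the sample size stays at 23 per group, 46 in total.

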## 7 Conclusion

This exploratory study provides preliminary observations on the potential of an integrative approach combining Cognitive Behavioral Therapy (CBT) and *Brahmi* in the context of Premenstrual Syndrome (PMS). The design does not permit causal interpretation or allow differentiation of the individual contributions of either intervention, and the findings should therefore be regarded as hypothesis-generating rather than definitive. Within these constraints, the study illustrates the feasibility of examining combined psychological and herbal strategies in women’s health and points to areas where further investigation is warranted. Future research, particularly studies with larger samples, diverse populations, and designs that test each intervention separately as well as in combination, will be essential to clarify their roles and establish a more robust evidence base.

## 8 Ethics and dissemination

### 8.1 Research ethics approval

The institutional ethics committee (IEC) meeting was held on 16/01/2025 at Amrita School of Ayurveda. 07 members attended the meeting. Ethics approval received on 19/01/2025.

Ref: IEC.ASA.PJR/06/25.

Letter no. IEC.ASA.PJR/06/25/APPROVAL.

### 8.2 Consent and assent

The principal investigator will present the trial details to the participants. Participants will furthermore receive informational brochures for participants. Participants will subsequently engage in an educated dialogue with the primary investigator. The principal investigator will secure written consent from subjects who agree to partake in the experiment. Patient information papers and informed consent forms are supplied to all participants in the trial. All informed consent documents and patient information sheets have been translated into English and Malayalam.

